*Crush the Crave* for vaping cessation was developed based on an earlier version of the app for smoking cessation [25-27]. An RCT of 1599 young adult smokers assessed *Crush the Crave* for smoking cessation and found that the 30-day point prevalence abstinence (PPA) at 6 months for the intervention condition (118/820, 14.4%) was not significantly different (odds ratio 0.82, 95% CI 0.63-1.08) from that for the control condition (132/779, 16.9%). However, the rate of abstinence was favorable when compared with the unassisted 30-day quit rates of 11.5% of young adults [28]. In addition, it was determined that 61% of the young adult smokers in the RCT were vaping. The increasing nicotine dependence and use of vapes among youth have prompted interest in developing an app for vaping cessation based on people’s experiences with *Crush the Crave* for smoking cessation. *Crush the Crave* is a tracker app that tracks the following information: the number of vape-free days and the amount of money saved since quitting vaping, as well as triggers and cravings. The app also provides the following functions: tailored supportive messages and inspirational graphic images for quitting vaping, personalized quit plans, graphic performance feedback, digital awards for achieving milestones, the reporting of vaping triggers, assistance for dealing with cravings, and links to other supportive resources that can aid in vaping cessation.

The primary aim of our study is to determine the effectiveness of the *Crush the Crave* app in supporting vaping cessation among youth recruited to the intervention arm via comparison with an assessment-only control group. The primary hypothesis is that participants in the intervention group—those using *Crush the Crave*—will be more likely to be abstinent at the 6-month follow-up point than participants in the assessment-only control arm. Our trial is currently open for recruitment. The anticipated completion date for our study is March 2024.

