#### Assessment-Only Control

Based on an approach that is similar to the one used by Graham and colleagues [8], participants will be invited via email to complete the baseline assessment, and they will be invited to complete the follow-up assessment questionnaires asking about e-cigarette use and abstinence (as outlined in the following sections) at 3, 6, 9, and 12 months. At the end of the intervention period and following the last follow-up assessment, they will be invited to try the *Crush the Crave* app, if they are interested.

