### Data Analysis Plan

#### Primary Outcome

Demographic and vaping characteristics (eg, vaping dependence, use of e-cigarettes, and self-confidence to quit) will be compared between groups at baseline. The intention-to-treat principle will be followed for statistical analyses, and all participants will be analyzed in the study arm to which they were randomized. Negative binomial regression with an identity function and robust SEs will be used to test between-group comparisons of the primary outcome variable—30-day PPA at follow-up. Multiple imputation via chained equations using the observed predictors of outcomes and the predictors of loss to follow-up will be performed to impute missing outcome data to correct for any potential bias caused by missing data. The imputation model will include age, sex and gender, education, marital status, province of residence, ethnicity, vaping dependence, self-confidence to quit, perceived stress, and the intervention group. The inverse of the adjusted risk difference will provide the number needed to treat.

The sample size of 600 (inclusive of both the control arm and the intervention arm) was selected to differentiate an effect size odds ratio of 1.60, assuming a base cessation rate of 5%, an α of .05, a power of 0.8, and a 75% (450/600) response rate.

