## Discussion

### Protocol Overview

This is the first-ever RCT study to evaluate the effectiveness of a smartphone app for supporting youth vaping cessation. The primary aim of our study is to determine the effectiveness of the *Crush the Crave* app in supporting vaping cessation among youth recruited to the intervention arm via comparison with an assessment-only control group. The primary hypothesis is that participants in the intervention group—those using *Crush the Crave*—will be more likely to be abstinent at the 6-month follow-up point than participants in the assessment-only control arm.

The *Crush the Crave* app was developed based on the best available evidence on vaping cessation and an empirical investigation on the effectiveness of an earlier version of the app for smoking cessation [22]. At the time of writing, 4 other clinical trial protocols for evaluating vaping cessation interventions among youth and young adults were registered on ClinicalTrials.gov. Of these, only 1 has been completed; the results are accessible in the published scientific literature and show that the intervention was successful (abstinence success rates of 16% for the intervention group and 8% for the control group) in encouraging young adults to stop vaping through an SMS text messaging program [8]. This study was useful in providing a benchmark for intervention effectiveness [8]. Of the 3 remaining protocols that are actively recruiting participants, 2 aim to evaluate the effectiveness of nicotine replacement therapy for vaping cessation among youth and young adults, and 1 aims to determine the effectiveness of a smartphone app called *Goal2QuitVaping*. Compared to the target sample size in our study (N=600), that of the Goal2QuitVaping study is relatively small (N=45).

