### Limitations

It is important to note the potential limitations in some aspects of the design and implementation of our trial. First, most notably, our trial was designed to include an assessment-only control group. We recognize that other app-based interventions for health are typically compared against other active controls or even other app-based interventions. Our methodology was adopted from the methodology used in the only completed trial (at the time of writing) of a technology-based vaping cessation intervention [8]. Second, our study focuses on evaluating the effectiveness of the intervention among youth and young adults who vape nicotine e-cigarettes. Given the recent rise in cannabis vaping among youth, interventions that focus on cannabis vaping will need to be developed and studied rigorously. Finally, we recognize that the active intervention is publicly available on the Apple and Google app stores and that participants in both trial groups may become aware of this fact during the trial. Cross-contamination measures will be put in place to assess awareness of and engagement with the *Crush the Crave* app among control group participants.

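### The claim of 80% power for an odds ratio of 1.60 fails at the assumed 5% control rate and at the 8% reported for the adopted vaping trial, and the two rates are not reconciled

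*Protocol article*

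**What the plan says.** The sample-size paragraph under Data Analysis Plan, Primary Outcome, sets the total of 600 to detect an odds ratio of 1.60. The remaining inputs are given there as follows: "assuming a base cessation rate of 5%, an α of .05, a power of 0.8, and a 75% (450/600) response rate". That leaves 225 responders per arm under the 1:1 allocation in Trial Design. No source or rationale accompanies the 5%, and the sidedness of the test is not stated.

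The article ties its control arm to one completed trial, a text-message vaping cessation programme. The Assessment-Only Control section opens "Based on an approach that is similar to the one used by" that trial. Limitations adds: "Our methodology was adopted from the methodology used in the only completed trial (at the time of writing) of a technology-based vaping cessation intervention". The Protocol Overview in the Discussion treats that trial as a benchmark for intervention effectiveness and reports "abstinence success rates of 16% for the intervention group and 8% for the control group". This 8% is the only control-group abstinence rate for vaping in the article.

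**The concern.** Two things in the plan do not fit together.

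- **The power statement.** The sample-size sentence gives every input needed to check it, and 600 (450 responders) looks far too small for an odds ratio of 1.60 at a rate as low as 5%.
- **The control rate.** The plan follows one trial's control approach and reports that trial's control rate, but sizes on a different rate without comment.

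The control rate matters because the primary result is an adjusted risk difference with a number needed to treat. An odds ratio of 1.60 means a difference of 2.8 points at 5% (number needed to treat about 36, from 1/0.0277) but 4.2 points at 8% (about 24, from 1/0.0421). The effect detectable with 450 responders moves with it too. A reader who takes the sentence at face value would think a non-significant result came from a trial well able to find a modest effect. That would be untrue at either rate.

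**Working it through.** **Inputs.** Odds ratio (OR) 1.60, control rate p1 = 5%, α = .05, power 0.8, 600 enrolled, 450 responders (Primary Outcome); 1:1 allocation (Trial Design); 8% vs 16% (Protocol Overview). Assumed here: a two-sided test and a two-proportion normal approximation.

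**Intervention rate implied by the OR.** p2 = OR·p1 / (1 − p1 + OR·p1).
- At 5%: 0.08/1.03 = 7.77%, difference d = 2.77 points.
- At 8%: 0.128/1.048 = 12.21%, d = 4.21 points.

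**Trying to reproduce 600.** With p̄ the mean of the two rates, n per arm = [1.960·√(2p̄(1−p̄)) + 0.842·√(p1(1−p1)+p2(1−p2))]² / d².
- At 5%: (1.960×0.3457 + 0.842×0.3452)² / 0.02767² gives 1,225 per arm, 2,450 evaluable, and 2,450/0.75 = 3,267 enrolled.
- Variants at 5% (evaluable / enrolled): one-sided 1,930 / 2,574; two-sided with continuity correction 2,592 / 3,456; one-sided with 1.6 read as a risk ratio (5% vs 8%) 1,668 / 2,224. A Wald test on the log OR and an arcsine calculation (both two-sided) need about 2,488 and 2,423 evaluable.

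None gives 450 evaluable or 600 enrolled. The two-sided requirement is 2,450/450 = 5.4 times the planned number of responders.

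**Power of the stated design, 225 per arm.** Power = Φ[(d − 1.960·SE0)/SE1], with SE0 = √(2p̄(1−p̄)/n) and SE1 = √((p1(1−p1)+p2(1−p2))/n).
- 5% vs 7.77%: (0.02767 − 1.960×0.02305)/0.02301 = −0.76, power 22%.
- 8% vs 12.21%: (0.04214 − 1.960×0.02842)/0.02835 = −0.48, power 32%.
- Best case over all control rates at OR 1.60: about 44% vs 55.7%, power 70%.

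Even at 8%, an OR of 1.60 needs 803 per arm, 1,606 evaluable and 2,142 enrolled.

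**What 225 per arm does detect at 80% power.**

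| Control rate | Intervention rate | Detectable OR |
|---|---|---|
| 5% | 12.4% | 2.70 |
| 8% | 16.7% | 2.30 |

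**Benchmark contrast, 8% vs 16%.** OR = (0.16/0.84)/(0.08/0.92) = 2.19. (0.08 − 1.960×0.03064)/0.03040 = 0.66, power 74%.

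**Sensitivity to the assumptions.**
- If all 300 per arm counted as fully observed, power for OR 1.60 would be 28% at 5% and 40% at 8%. It would reach 80% only with a control rate of about 34% or more.
- One-sided with 225 per arm, power is 33% at 5% and 44% at 8%. It just touches 80% at a control rate near 44%.

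**The case against.** The strongest case on the other side concerns the control rate.

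- **A reader might infer that 5% is wrong, or that the plan sizes for a control arm it is not running.** The documents do not support this. The true rate is unknown. The 8% comes from US participants aged 18 to 24, and the article gives neither its abstinence definition nor its time point. This trial takes Canadians aged 16 to 29 from an existing panel on the basis of any nicotine vaping in the past 30 days, with no stated requirement that they want to quit. A rate below 8% is plausible. What was adopted is the assessment-only approach, and the benchmark label is attached to intervention effectiveness. This stands.
- **A reader might also cite the other rates in the Introduction, 11.5% and 16.9%, as showing that 5% is too low.** Both belong to smoking. The article says of the smoking app that "the rate of abstinence was favorable when compared with the unassisted 30-day quit rates of 11.5% of young adults", and 16.9% is the control arm of that smoking trial. Neither is evidence about vaping cessation here.
- **At a fixed OR, 5% is the conservative choice.** Moving to 8% cuts the required enrolment from 3,267 to 2,142. This stands, so the choice of control rate is not what breaks the sizing.
- **The article is condensed, and the rationale for 5% may be in a fuller document.** This stands too, so the request on the rate is for a justification.

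None of this rescues the power statement. The article gives its inputs in full, and they do not produce the stated result.

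**Conclusion.** The concern holds in this form: the claim of 80% power for an OR of 1.60 with 600 enrolled and 450 responders is wrong as written. Power is about 22% at the plan's own 5% and about 32% at the 8% of the adopted trial. At 225 per arm, two-sided, it cannot exceed about 70% at any control rate. The gap between 5% and 8% is unexplained and needs a justification, but it is not shown to be an error.

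The figures assume a two-sided .05 test, the normal approximation and 225 analysed per arm. At the two rates in question, a one-sided test or counting all 600 as observed changes the figures but leaves power far below 80%. Using the 8% also assumes that it was measured by an abstinence definition close to this trial's, which the article does not let a reader check.

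**What to change.** In the sample-size paragraph, at unchanged enrolment:

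1. Keep 5% on record as the value used when 600 was chosen, and add the reason for it, set against the 8% (for example differences in age range, country, recruitment source, or abstinence definition and time point, as far as these apply).
2. Withdraw the statement of 80% power for an OR of 1.60. Say instead that 450 responders give 80% power, two-sided .05, for an OR of about 2.70 at a 5% control rate (5% vs 12.4%) and about 2.30 at 8% (8% vs 16.7%), with about 74% power for 8% vs 16%.
3. State the sidedness of the test.
4. Leave the 11.5% and 16.9% smoking rates out of the argument for the control rate.

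This costs a rewrite of one paragraph, with no extra participants or data. The downside is that the trial must say openly that it can detect only effects well above an OR of 1.60. Keeping 1.60 as the target would instead need about 3,267 enrolled at 5% or 2,142 at 8%.

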Previous work in intervention research and development identified technology-based interventions as a promising area for promoting youth vaping cessation [6]. Smartphone technology and mobile software apps are highly accessible, easily scalable, and cost-effective platforms for mental health interventions [15]. Globally, young people born after the year 2000 are the top smartphone users [16,17]. Consequentially, vaping prevalence is also greatest among those aged 18 to 24 years and 15 to 17 years [11,18,19]. In fact, the use of apps for addressing mental health and substance use among youth is well documented in the literature [20-23], with apps for vaping cessation being among the latest additions [24]. However, there is currently no empirically tested smartphone app that specifically targets youth vaping cessation [24].

This protocol describes one of the first-ever randomized controlled trial (RCT) studies to evaluate the effectiveness of an app-based intervention for supporting vaping cessation among youth. The first-ever RCT of a vaping cessation intervention was designed to evaluate the effectiveness of an SMS text messaging program called *This is Quitting* in helping young adults in the United States aged 18 to 24 years to stop vaping [8]. The trial results showed that an SMS text messaging program that provided interactive and tailored messages was successful in promoting vaping cessation among young adults [8]. However, this trial did not include youth aged 14 to 17 years, for whom vaping cessation is urgently needed, as participants [1,4,18]. In our study, 600 youths (aged 16-18 years) and young adults (aged 19-29 years) who vape will be recruited. The intervention is called *Crush the Crave*—a comprehensive, full-featured app for supporting youth vaping cessation (Figure 1).

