## Methods

### Trial Design

A 2-arm, single-blind, parallel RCT will be conducted over 12 months. Study invitations will be sent to 600 youth and young adult e-cigarette users and randomized between an intervention arm, which will be using *Crush the Crave* (n=300), and an assessment-only control arm (n=300) in a 1:1 ratio. The trial protocol is registered with the Center for Open Science (registration digital object identifier: 10.17605/OSF.IO/HMD87). The trial protocol was developed in accordance with the SPIRIT (Standard Protocol Items: Recommendations for Interventional Trials) 2013 checklist of recommended items for interventional trials [29].

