### Informed Consent

After eligibility screening, participants must provide informed consent to proceed with study enrollment. The web-based consent form contains information about the study, the *Crush the Crave* app, participant eligibility, requirements and expectations for study participation, compensation, data collection, and plans for protecting participants and their privacy (ie, data deidentification), as well as the contact information of study staff and the University of Toronto Office of Research Ethics. Those who agree to participate in the study will receive an email containing a link to download the *Crush the Crave* app (sent to the email addresses they provided).

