### Randomization

Eligible participants will be identified from the Vaping Dependence Cohort. The *rand()* function in Excel (Microsoft Corporation) allowed for simple randomization; the top 50% highest numbers identified the participants that will receive invitations to use the *Crush the Crave* app. A research assistant from the Vaping Dependence Cohort will conduct the randomization and create a variable with a blinded key for the initial data analysis, which will allow the investigators and analyst to be blinded to the group allocation up until the data analysis is complete.

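### The protocol uses 600 both for people invited and for people recruited, and does not say which stage its single 75% response rate covers, so the 450 expected outcomes cannot be verified

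*Protocol article*

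**What the plan says.** The number 600 appears in two roles.

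- **Invited and randomized.** Trial Design: "Study invitations will be sent to 600 youth and young adult e-cigarette users and randomized between an intervention arm", with 300 per arm. The Methods paragraph of the Abstract says the same.
- **Recruited, or the target.** Introduction: "600 youths (aged 16-18 years) and young adults (aged 19-29 years) who vape will be recruited". The Protocol Overview in the Discussion opens its comparison with another app trial: "Compared to the target sample size in our study (N=600". The Primary Outcome section of the Data Analysis Plan gives "The sample size of 600 (inclusive of both the control arm and the intervention arm" as the number behind the power claim.

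That section makes one allowance for loss, "a 75% (450/600) response rate", and does not name the stage.

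Two other sections describe the path from panel to enrolment. Under Randomization, a random number is attached to eligible panel members, and "the top 50% highest numbers identified the participants that will receive invitations to use the" app. Under Informed Consent, "After eligibility screening, participants must provide informed consent to proceed with study enrollment".

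**The concern.** An invited panel member contributes an observed outcome only after passing screening, consenting, and answering the follow-up survey. Loss can therefore occur both before and after enrolment. A count of invitees and a count of enrollees agree only if everyone invited enrols, so using 600 for both is an inconsistency in the number on which the power statement is built.

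The single 75% does not settle it. If it is follow-up response, Trial Design as worded reaches 450 only with complete uptake. If it is response to the invitation, nothing is allowed for loss to follow-up, although the same section plans multiple imputation for that loss.

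The analysis set is affected too. The Randomization section suggests that allocation comes before invitation, and so before consent. The intention-to-treat set could then be all randomized invitees or only those who consented. The choice changes the denominators, the amount of imputation, and the sensitivity analysis that counts nonresponders as vapers. If only consenters are analysed, consent given after allocation could differ between arms.

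**Working it through.** **Inputs from the document.** 600 in total, 1:1 allocation, 75% response, control abstinence 5%, odds ratio 1.60, α 0.05, power 0.80 (Trial Design; Data Analysis Plan, Primary Outcome). The sidedness of α is not stated; two-sided is used below unless noted.

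**Assumption.** Enrolment among invitees (u) is not given. It is shown at 100%, 75% and 50%.

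**1. The plan's own figure.** 600 × 0.75 = 450. The arithmetic is right.

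**2. What 450 means under each reading.**

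| 600 counts | 75% covers | Expected outcomes |
|---|---|---|
| Enrolled | Follow-up | 600 × 0.75 = 450 |
| Invited | Invitation through to outcome | 600 × 0.75 = 450 |
| Invited | Follow-up only | 600 × u × 0.75 |
| Invited | Uptake only | 450 enrolled, less any follow-up loss |

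The first two rows give 450. Only the last two can give fewer.

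**3. Size in the third row.**
- u = 100%: 600 × 1.00 × 0.75 = 450
- u = 75%: 600 × 0.75 × 0.75 = 337.5, about 338
- u = 50%: 600 × 0.50 × 0.75 = 225

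Conversely, enrolling 600 would take 600/0.75 = 800 invitations at 75% uptake and 600/0.50 = 1200 at 50%.

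**4. Power at each number.** The intervention rate implied by the odds ratio is p2 = 1.6 × (0.05/0.95) / [1 + 1.6 × (0.05/0.95)] = 0.0777, a difference of 0.0277. With n per arm,

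power = Φ{ [0.0277√n − 1.96 √(2p̄(1−p̄))] / √(p1(1−p1) + p2(1−p2)) }, where p̄ = (p1 + p2)/2 = 0.0638.

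The two square roots are 0.3457 and 0.3452. At n = 225 the argument is (0.415 − 0.678)/0.345 = −0.76, so power is 22%.

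| Outcomes | Power for OR 1.60 | OR detectable with 80% power |
|---|---|---|
| 450 | 22% | 2.70 (5% vs 12.4%) |
| about 338 | 18% | 3.06 (5% vs 13.9%) |
| 225 | 13% | 3.75 (5% vs 16.5%) |

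**5. Separating the two faults.** The first row has no enrolment loss, yet power is 22%, not 80%. A one-sided test at 450 gives 33%. The stated inputs need 1225 per arm, 2450 outcomes, for 80% two-sided power. The gap from 80% to 22% therefore comes from the sample-size inputs. The ambiguity over 600 accounts only for any further fall, from 22% to 18% or 13%, under the assumed enrolment.

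**The case against.** Much of the text favours 600 enrolled. The Introduction speaks of recruitment, the Discussion of a target sample size, and the Primary Outcome section of a sample size across both arms. Secondary Outcomes uses nonresponder for someone without outcome data, which fits 75% as follow-up response. The Trial Design sentence is grammatically awkward and may be loose wording. On that reading 450 is exact. The imputation model uses items from the baseline survey, such as self-confidence to quit and perceived stress, which points to an analysis set of baseline completers. A condensed article may also leave the uptake rate and the number approached to the full protocol.

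Most of this stands, and it limits the point. A reader might infer that the design will fall below 450 outcomes under any ordinary enrolment. The document does not support that, because two of the four readings deliver 450 and no uptake rate is given. A reader might also attribute the low power to confusion over invitations. That does not follow either, since power is already 22% with all 450. The absence of an uptake rate is not itself a finding.

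The contradiction remains. The invitation wording is in both the Abstract and Trial Design, and the Randomization section, where random numbers decide who is invited to the app, is compatible with it. The invited reading cannot be excluded, and if only 600 are invited, the 600 target is missed at any uptake below 100%.

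**Conclusion.** The point holds as an internal inconsistency in the sample-size statement, not as an arithmetic error. The document gives 600 two meanings and applies one loss allowance of unstated scope, so 450 cannot be checked against the design described.

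Its size is conditional. There is no shortfall if 600 are enrolled or if 75% is the end-to-end rate. If 600 are invited and 75% is follow-up response alone, expected outcomes are about 338 or 225 at assumed enrolment of 75% or 50%, and power for the stated effect falls by roughly 4 to 9 percentage points from 22%. Which case applies cannot be determined from the document. Resolving it would not repair the power claim, which fails at 450 for a separate reason.

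**What to change.** - In the Abstract, Trial Design and Primary Outcome sections, state what 600 counts, in the same terms throughout.
- Give the number invited separately from the number enrolled.
- Say which stage 75% covers: uptake, follow-up at the primary time point, or both combined.
- State whether allocation comes before consent, and name the intention-to-treat set as all randomized invitees or those who consent.
- Restate the expected number of outcomes on that basis, and the power or detectable effect that follows. If 600 is the number invited and 75% is not end-to-end, replace 450 with 600 × expected enrolment × expected follow-up response. If 450 stands, the stated inputs support about 22% two-sided power for an odds ratio of 1.60, or 80% power for about 2.7.

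The cost is a few sentences and a less favourable power statement. The restatement itself needs no extra participants. Enrolling 600 when only 600 were to be invited would need more invitations, a separate decision for the sponsor given that recruitment had already begun.
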